### Composition of sample

The required sample size was determined for the primary outcome variable, that is, overall score of the Fibromyalgia Impact Questionnaire (FIQ). According to Bennett *et al*. [20], a clinically relevant change is a 15 to 20% reduction in the total FIQ score (which is equal to an approximate 10 to 15 points reduction). Assuming a unilateral alternative (that is, the intervention reduces the impact of fibromyalgia), we can detect differences of at least 15% with a power of 95% and α of 0.05 with two groups (intervention and usual control group) of 45 participants, with a mean in the FIQ of approximately 70 and a standard deviation of approximately 20 points. Assuming a maximum loss of follow-up of 30%, we will recruit a total of 60 women with fibromyalgia for each group. We will recruit a total of 120 women with fibromyalgia (that is, one LLLT intervention group and control group of 60 persons each).

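### Sixty per group does not cover the assumed 30% loss: it leaves 42 per group, not the 45 in the power statement, and covers at most 25%

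*Protocol article*

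**What the plan says.** The sample-size paragraph (Protocol article, Composition of sample) gives three figures that have to agree.

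- The number needed for the power statement: "with two groups (intervention and usual control group) of 45 participants". This comes "with a power of 95% and α of 0.05", under a one-sided alternative, with a mean score on the Fibromyalgia Impact Questionnaire (FIQ) of about 70 and an SD of about 20.
- The allowance for loss and the resulting target: "Assuming a maximum loss of follow-up of 30%, we will recruit a total of 60 women with fibromyalgia for each group".
- The total, 120, made up of "one LLLT intervention group and control group of 60 persons each".

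The paragraph gives no inflation formula and no other reserve. The abstract and the section on composition of groups and randomization repeat 120 patients and 60 per group.

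**The concern.** Forty-five per group is offered as the number that delivers the stated power, and 60 as the number to recruit so that loss of up to 30% is allowed for. Read in the ordinary way, 60 less 30% should leave at least 45. It does not.

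What is at stake is the retention threshold. Anyone following retention would take 30% as the loss at which the planned number still holds, when the planned number is already gone once loss passes 25%. The 45 also has almost no slack: on the basis where it reproduces, it gives just over 95% power, so any fall below 45 undoes the 95% figure.

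**Working it through.** **Inputs**, all from Composition of sample: 45 per group for the power statement; maximum loss 30%; 60 recruited per group; one-sided α 0.05; power 95%; mean FIQ about 70; SD about 20; clinically relevant change 15 to 20%. In points, 15% of 70 is 10.5 and 20% of 70 is 14.

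**Step 1: where 45 comes from.** Normal approximation for two means, n per group = 2 × (z for α + z for power)² × SD² / difference², with both z values 1.645.

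- 14 points: 2 × (3.29)² × 400 / 196 = 44.2, so 45. The stated figure reproduces.
- 10.5 points: 2 × (3.29)² × 400 / 110.25 = 78.5, so 79. The stated figure does not reproduce.

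So 45 corresponds to the upper end of the 15 to 20% range. That the text attaches it to 15% is a separate problem. Here 45 is taken as given.

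**Step 2: the loss allowance.** The number to recruit is the number needed divided by the fraction retained.

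- Needed at 30% loss: 45 / (1 − 0.30) = 64.3, so 65 per group and 130 in total.
- Left from 60 at 30% loss: 60 × 0.70 = 42.
- Largest loss that still leaves 45 from 60: 1 − 45/60 = 25%.

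The stated 60 is 5 per group short of 65 (10 in total), which is too much for rounding.

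**Step 3: what the shortfall costs.** Power of a one-sided two-sample t test at α 0.05, from the noncentral t distribution with 2n − 2 degrees of freedom and noncentrality difference / (20 × √(2/n)):

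| Difference | 45 per group | 42 per group | Fall |
|---|---|---|---|
| 14 points (20% of 70) | 95.1% | 93.8% | about 1.3 points |
| 10.5 points (15% of 70) | 79.6% | 77.1% | 2.5 points |

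The normal approximation gives nearly the same: 95.3% to 94.1%, and 80.1% to 77.7%. Put another way, the difference detectable with 95% power, (1.645 + 1.645) × 20 × √(2/n), moves from 13.9 points at 45 per group to 14.4 at 42.

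**The case against.** The strongest reply is that almost nothing turns on this. On the basis where 45 reproduces, power drops by little more than one point. The detectable difference moves by about half a point, against a mean and an SD that the text itself calls approximate. The shortfall begins only if loss passes 25%, and the protocol calls 30% a maximum. All of that stands, and it limits the weight of the point. It does not make the figures agree.

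A second reply is that the intention-to-treat analysis (Evaluation of results) keeps everyone in. It does not supply outcomes for patients who are lost, and the sample-size paragraph itself raises the number recruited because of loss.

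Three stronger readings are tempting, and the document does not support them.

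- A reader might infer that the loss allowance is what takes power down to 77%, or to 66% if the test is made two-sided. Those figures are low mainly because 45 per group already gives only 79.6% one-sided (69.3% two-sided) for 10.5 points. The loss allowance accounts for 2.5 and 3.1 points of it. The two-sided figures also leave the protocol's stated basis.
- A reader might infer that 60 came from multiplying by 1.30. But 45 × 1.30 = 58.5 rounds up to 59, not 60, and no formula is given. It is a possible explanation, no more.
- A reader might say that the protocol promises undiminished power at 30% loss. It does not say so in words. That is a fair inference from setting 45, 30% and 60 side by side.

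**Conclusion.** The point holds as an arithmetic inconsistency: 45 evaluable, 30% loss and 60 recruited per group cannot all be right. Sixty covers at most 25% loss and leaves 42 at 30%; holding 45 at 30% would take 65 per group.

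The size is small: three fewer evaluable patients per group, and about 1.3 points of one-sided power for 14 points, or 2.5 for 10.5 points. The counts follow from the protocol's own figures alone. The power figures rest on further assumptions: equal loss in both groups, SD exactly 20, and a plain two-sample t test on FIQ. The Statistical analysis section plans a repeated-measures ANOVA, and Evaluation of results lists FIQ as secondary, so the percentages show scale and are not precise predictions.

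It is wrong as written and cheap to correct. It is not a reason to enlarge the trial.

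**What to change.** Keep 120 patients and restate the sentence, for example: *Sixty per group allows for up to 25% loss to follow-up (45 evaluable per group); at 30% loss, 42 per group remain.*

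Leave power figures out of this sentence for now. The preceding sentence claims 95% power for a difference of at least 15%, which is 10.5 points on a mean of 70. Putting 77% for the same difference next to it would create a new contradiction. Quote power at 42 per group only together with the separate correction of that 95% statement, for the same difference and the same sidedness.

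The cost is one sentence and a slightly less favourable stated tolerance for loss. No patients are added and the design does not change, which suits a trial that was already recruiting when the article was submitted (Trial status).

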### Inclusion criteria

The following criteria will be adopted as requirements for inclusion in the study:

•A clinical diagnosis of fibromyalgia based on ACR criteria;

•Cognitive level sufficient for understanding the procedures and following the instructions;

•Agreement to participate in the study and the signing of a statement of informed consent after receiving clarifications regarding the objectives of the study.

### Exclusion criteria

Patients with the following will be excluded from the study:

•Psychiatric disorders, history of drug abuse or other behavior that requires psychiatric medication intervention;

•Development of situations beyond clinical control that do not allow participation in aerobic training activities, exertion or group activities;

•Severe physical disability;

•Co-morbid condition (irritable bowel syndrome, intestinal cystitis, and others);

•Uncontrolled endocrine disorders;

•Although there is no description of serious complications in individuals submitted to LLLT, those with a history of epilepsy, seizures, heart disease, arrhythmia, pacemaker, undiagnosed pain, pregnancy and malignant tumors will be excluded from the study.

### Composition of groups and randomization

After the initial evaluation, the 120 volunteers will be randomly allocated to an intervention group (LLLT; n = 60) or control group (CLLLT; n = 60). Randomization numbers will be created using a randomization table at a central office, where a series of sealed, opaque, numbered envelopes will be used to ensure confidentiality. Each envelope will contain a card indicating the group in which the patient will participate. After fulfilling the eligibility criteria, a clinical evaluation and assessments of pain and sleep quality will be carried out and self-administered quality of life questionnaires will be applied (Fibromyalgia Impact Questionnaire, Medical Outcomes Study 36-item Short-Form Health Survey and McGill Pain Questionnaire). After the volunteer signs the statement of informed consent, she will randomly select one of the envelopes. This study received approval from the UNINOVE Human Research Ethics Committee (protocol number 474921). Additionally, the study is registered with the World Health Organization Universal Trial Number (UTN) U1111-1125-5007 and the Brazilian Registry of Clinical Trials (number - RBR-42gkzt).

### Blinding procedures

A single examiner with the necessary skills will perform the evaluations in order to achieve reproducible examinations and more reliable results. A second examiner will be trained to administer the laser and conduct the exercises. A third examiner will perform the re-evaluations of the two groups. The groups will not be identified in order to avoid ‘unmasking’ during the study.

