## Experimental protocol

### Evaluation and educative session

The evaluations will occur prior to and at the end of the therapeutic program by a researcher with no knowledge regarding the type of treatment to which the subjects will be submitted. All subjects in both groups will be submitted to the same evaluation protocol, which will include the aspects listed below.

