#### Pressure algometry of pain threshold

A pressure algometer (digital algometer, model DDK 20, manufactured by Kratos Ltd., Cotia, Sao Paulo, Brazil) is a device that assesses the pain threshold. This device consists of a round rubber disk (1 cm^2^) attached to a pressure (force) gauge. The gauge displays values in kilograms. Because the surface of the rubber tip is 1 cm^2^, the readings are expressed in kilogram per square centimeter (kg/cm^2^). The range of the algometer is 0 to 10 kg and records in 0.1 kg divisions. At one end of the device, perpendicular pressure is applied to the surface of the skin and recorded using a manometer. The algometry of the pain threshold on the tender points will be performed based on the fibromyalgia classification criteria of the ACR, following the procedures described below:

•The patient will be asked to sit in a chair with feet supported on the ground and hands supported on the lap;

•The tender points will be marked with a skin marking pen and evaluated bilaterally in the following order: occipital, anterior lower cervical, trapezius, supraspinatus, second costochondral joint, lateral epicondyle and medial edge of the knee;

•The patient will be instructed to remain in an orthostatic position and the tender points of the gluteus and greater trochanter will be marked with the pen, bilaterally;

•During the assessment of the pain threshold on the tender points, perpendicular pressure will be applied to the surface of the skin and increased gradually in increments of 0.1 kg until the patient reports feeling pain;

•Positive results will be those below 2.6 kg/cm^2^, which is equivalent to the 4.0 kg/cm^2^ described in studies by Wolfe *et al*. [21].

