### Low-level laser therapy

#### Specifications

The Twin Laser (MM Optics Ltda., São Carlos, São Paulo, Brazil) will be employed, the active medium of which is made up of a Gallium-Aluminum-Arsenide semiconductor diode, with emission in the 780 nm near infrared wavelength (invisible) and variable power values in the continuous emission mode. The display provides the doses according to the power and application time. The laser will undergo verification of functioning, energy source, points of application and measurement of power.

To provide the ‘blinding’ of the study, the laser equipment has two identical application points furnished by the manufacturer - one active and the other a placebo (that does not emit energy); both have a sound device and guide light. The points will be named A and B by a researcher who will not participate in the treatment or evaluations. The researcher performing the applications and the evaluators will be unaware of which points received the effective dose and which received the placebo. The patients will also not have access to information regarding to which group they belong. The points will be identified only at the end of the data acquisition phase.

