### Evaluation of results

The intention-to-treat analysis will be followed. The patients will be evaluated with regard to the primary outcome (pain) using the visual analog scale for pain, the McGill Pain Questionnaire and pressure algometry. The secondary outcome (quality of life) will be assessed using the SF-36 and FIQ. The use of medication will be controlled throughout the study. The data on the use of analgesics and daily dosage of adjuvant therapy, such as antidepressants and muscle relaxers, will be recorded and tabulated.

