### Statistical analysis

ANOVA test with repeated measurements for the time factor will be performed to test between-groups differences (followed by the Tukey-Kramer post hoc test), and a paired *t* test will be performed to test within-group differences. The level of significance for the statistical analysis will be set at 5% (*P* ≤0.05).

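### Baseline and end-of-program pressure algometry are assigned to different examiners, so within-group change in this primary pain measure cannot be separated from a change of examiner

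*Protocol article*

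**What the plan says.** Blinding procedures in the protocol article divides the work among three people. The first: "A single examiner with the necessary skills will perform the evaluations in order to achieve reproducible examinations and more reliable results". The next has treatment duties only: "A second examiner will be trained to administer the laser and conduct the exercises". The last sees patients at the end: "A third examiner will perform the re-evaluations of the two groups".

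Evaluation and educative session sets two evaluation times: "The evaluations will occur prior to and at the end of the therapeutic program by a researcher with no knowledge" of the treatment type. Specifications, under Low-level laser therapy, adds that "The researcher performing the applications and the evaluators will be unaware of which points received the effective dose".

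Pressure algometry is operated by hand, with perpendicular pressure "increased gradually in increments of 0.1 kg until the patient reports feeling pain". Evaluation of results makes algometry one of three instruments for the primary outcome, pain, beside the visual analog scale and the McGill questionnaire.

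Statistical analysis plans a repeated-measures ANOVA with a time factor to compare the groups, and "a paired *t* test will be performed to test within-group differences".

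**The concern.** The stated reason for a single examiner is reproducibility. That reason matters most when a patient's end value is compared with the same patient's baseline, and this is where the arrangement changes the examiner.

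A pressure pain threshold can depend on how fast the examiner presses, at what angle, and how the patient is prompted. If the two examiners differ systematically, the difference enters every patient's change score. A paired t test would report it as improvement or worsening. The Discussion expects the pressure pain threshold to rise in the laser group, so a within-group rise in algometry is a result that readers will look for. Because the examiners do not overlap at either visit, the trial data hold no information from which the shift could be estimated and removed from the time effect.

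**Working it through.** **Step 1: who measures when.** The plan states no figure here, so there is none to reproduce. Setting the sections side by side:

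| Visit | Laser group | Control group |
|---|---|---|
| Before the program | First examiner | First examiner |
| End of the program | Third examiner | Third examiner |

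Examiner and visit are the same factor. The first and third examiners' roles come from Blinding procedures, and the two visits from Evaluation and educative session.

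**Step 2: model.** Let b be the third examiner's reading minus the first examiner's, taken as constant. For group g:

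observed mean change in g = true mean change in g + b

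- Within a group, the paired t test estimates true change + b. The ANOVA time main effect contains b in the same way.
- Between groups: (true change, laser + b) − (true change, control + b) = true change, laser − true change, control. The shift cancels.

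**Step 3: size within a group.** Inputs:

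- n = 60 per group, as recruited (Composition of sample). With the full 30% loss allowed there, n = 60 × 0.70 = 42.
- Two-sided α = 0.05 (5% level from Statistical analysis).
- True change = 0, to isolate the effect of the examiner.
- Shift b: **assumed**, 0.1 to 0.5 kg/cm². The algometer records in 0.1 kg divisions on a 1 cm² tip, so this is one to five steps.
- SD of change: **assumed**, 0.8 to 1.2 kg/cm².

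The paired t statistic follows a noncentral t distribution with n − 1 degrees of freedom and noncentrality

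δ = b / (SD / √n).

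Example: b = 0.3, SD = 1.0, n = 60 gives δ = 0.3 × √60 / 1.0 = 2.32. With a critical value of 2.00 on 59 degrees of freedom, the probability of significance is 0.63.

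Probability that the paired test is significant when nothing has changed, n = 60:

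| Shift b (kg/cm²) | SD 1.2 | SD 0.8 |
|---|---|---|
| 0 | 0.05 | 0.05 |
| 0.1 | 0.10 | 0.16 |
| 0.2 | 0.25 | 0.48 |
| 0.3 | 0.48 | 0.82 |
| 0.5 | 0.89 | 1.00 |

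At n = 42, a shift of 0.1 gives 0.08–0.12 and a shift of 0.3 gives 0.35–0.66.

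**Step 4: between groups.** Simulation (20,000 runs per setting, 45 and 60 per group, common shift of 0 to 0.5 SD of change, no true effect) gave a rejection rate of 4.6% to 5.2% for the two-sample test on change, with a mean difference of about zero. This agrees with the cancellation in Step 2.

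**The case against.** The strongest reply is that the comparison that matters is unharmed. A reader might infer from the change of examiner that the laser-versus-placebo effect is itself confounded. The documents do not support this. The third examiner re-evaluates both groups, the applicators are coded A and B by someone outside treatment and evaluation, and the evaluators do not know which is active. A constant shift is therefore common to both groups and cancels. This stands in full.

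Other replies, and what remains of each:

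- *Within-group change could not be credited to the laser anyway.* Both groups also receive supervised exercise, and the educative session with its home exercises. True, and it limits the weight of the point. But the paired tests are planned and will be read, and the examiner shift is one source of error that the design can avoid.
- *The offset is assumed, and the procedure is standardized.* The device is digital, the tender points are marked, and order and posture are set. A small shift is plausible, so the table starts from zero. At one step the rate is already two to three times the nominal 5%.
- *The exposure is narrow.* Patients mark the visual analog scale themselves, polysomnography is scored by a specialized reader, and the FIQ, SF-36 and McGill are described as self-administered. Help with reading leaves some room for prompting, but the point is essentially about algometry.
- *The sections do not clearly conflict.* A reader might take Evaluation and educative session to say that one person does both visits. Its singular researcher mainly describes blinding, and Specifications uses the plural for evaluators. The wording should be aligned, but it is not a firm contradiction.
- *A fresh assessor at the end is a defensible blinding choice.* It is, but the A/B coding already protects an evaluator who stays away from allocation and treatment.

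**Conclusion.** The point holds in a limited form. For pressure algometry, examiner and visit are completely aliased, so the within-group paired t tests and the ANOVA time effect cannot separate true change from an examiner shift. With no true change, the chance of a significant within-group result at 60 per group rises from 5% to somewhere between 10% and nearly 100% over shifts of 0.1 to 0.5 kg/cm². The shift and the SD of change are both assumptions; the aliasing does not depend on them.

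It would go too far to say that no analysis can deal with the shift. That is true of the time effect, whereas the group-by-time contrast removes a constant shift. What could remain in the laser-versus-placebo contrast is extra noise, if the examiners' difference varies by patient or by pain level. The documents give nothing from which to size that, and it is not quantified here. This is an inexpensive improvement to the design and no threat to the main comparison.

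**What to change.** In Blinding procedures, have the same blinded evaluator carry out both visits of each patient, and keep that evaluator away from allocation and the treatment sessions. If workload needs two evaluators, give each patient one evaluator for both visits. Word Evaluation and educative session to match.

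Trial status says that recruitment has started. For patients already evaluated under the present arrangement, record which examiner took each measurement, and base algometry conclusions on the between-group contrast, not on within-group change.

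The cost is a change of wording and of the evaluators' rota, with no added staff. The downsides are less flexible scheduling and a trial that mixes two evaluation arrangements.

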## Experimental protocol

### Evaluation and educative session

The evaluations will occur prior to and at the end of the therapeutic program by a researcher with no knowledge regarding the type of treatment to which the subjects will be submitted. All subjects in both groups will be submitted to the same evaluation protocol, which will include the aspects listed below.

#### Personal data

Age (in years), body mass (in kilograms), height (in meters), profession, schooling (no schooling, elementary education, high school education, university education, postgraduate education) and marital status.

#### History of pain

Duration of pain, sites of pain in decreasing order of intensity, period of day in which pain is more intense, factors of improvement and worsening of pain, sleep quality, type of mattress and pillow.

#### Visual analog scale for pain

A visual analog scale will be used for the assessment of pain intensity, consisting of a straight line measuring 10 centimeters, with no numbers displayed and on which the words ‘no pain’ appear on the left extremity and ‘unbearable pain’ appear on the right extremity. The patient will be instructed to mark a point on the line that indicates the intensity of pain she is feeling at the time. Higher scores denote greater pain intensity.

